#### The chat sessions

Several chat sessions will be available every week based on the previous schedule. A participant who wants to ask specific personal questions can register for a pre-scheduled session and log in on the day and time determined. The specialist conducting the chat session is a master’s or PhD level psychologist with more than 3 years of clinical experience with pre- and post-bariatric patients. The psychologist assigned to the session will be online for 30 minutes to chat with registered participants. Patients are allowed to schedule a session every other week. All of the psychologists who are involved in the chat sessions are under frequent supervision at the University of Minho.

## Objectives of the study and expected outcomes

The specific objectives of this project are the following:To test the short- and long-term efficacy of the program in preventing weight regain and promoting weight loss maintenance, promoting new eating behaviors, decreasing psychological distress, enhancing individual self-concept, and addressing other psychological outcomes.To test the utility, feasibility, and perceived satisfaction with APOLO-Bari in terms of compliance with proposed tasks, log-in frequency, and direct evaluation of the satisfaction of participants. Participants with higher log-in frequency and compliance with monthly assessments are expected to report better weight outcomes, higher levels of satisfaction with weight loss and surgical treatment, and lower scores on the self-reported measures, thus reflecting better psychosocial functioning.To study weight regain by exploring the temporal courses of eating-related features and predictors of weight regain. We expect to identify fluctuations in key behaviors that precede weight regain.

## Methods/design

### Design and procedures

This a randomized controlled trial (Current Controlled Trials: ISRCTN37668662), with a superiority design that includes two parallel groups: a treatment-as-usual control group and an intervention group, who receive both treatment as usual and the internet-based program. Consecutive participants will be recruited from two hospital centers in the North of Portugal. Information about the hospital centers involved can be found on the current controlled trials website for our trial registration number.

All participants will be contacted by phone or during their medical appointment and screened for the inclusion and exclusion criteria. Patients meeting these criteria will be invited for an orientation group session to inform them of the program and study procedures. The study will be introduced as a program to support bariatric patients remotely in the long term, which aims to monitor relevant variables and investigate patients’ perception of the utility of these interventions.

### Retention and incentives for the participants

The following strategies will be used to minimize attrition. First, there will be a financial incentive: the participants will receive a €20 voucher to use in a main retail chain store after completing the program. To be eligible for this reward, the participants must complete at least 70 % of their required assessments. Second, the participants will be asked for two contact phone numbers or email addresses at registration. Third, reminder emails will be sent every time a questionnaire or activity is available. Finally, an orientation session will be held before the beginning of the intervention.

### Informed consent and randomization

Those who agree to participate in the study will have a computer connected to the internet, and each participant will complete the informed consent form online and register in the program by creating a personal username and password. All participants will complete an initial short sociodemographic and clinical questionnaire (see details in the measures section). To ensure concealment of allocation, the APOLO-Bari system will then automatically randomize (computer-generating random numbers) the participants on a 1:1 basis, matching for age, sex, and surgery type.

After randomization, intervention group members will receive full access to the three components of the APOLO-Bari program in their personal accounts. The intervention will last for 12 months, and a 6-month period will follow, with no program access possible. During the intervention period, the system will record data on log-in frequency, task submission, and weekly monitoring from the intervention group.

The control group will only have access to general information on obesity and bariatric surgery and to the set of self-report measures at the different assessment times. The control group participants will be informed of the assessment times and the possibility of accessing the full program after the study is complete. Both groups will receive reminder emails every time a questionnaire or activity is available.

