#### Anthropometric measures

Participants will be instructed to report their weight based on a standardized assessment self-reported using the same scale on the same day of the week under the same conditions (the time of day and without clothes). The program will ask participants to report their weight once a month in one of their weekly assessments as part of their self-monitoring tasks. Both the intervention group and the control group will have their height and weight measured by the research team at baseline (*T*_b_), at 4- and 8-months midterm assessment (*T*_m4_, *T*_m8_), at the end of the intervention (final; T_*f*_), and at 6- and 12-months follow-up (*T*_fu6_, *T*_fu12_). The weight history of participants (e.g., highest and lowest weight since adulthood, pre-surgery weight, and lowest weight since surgery) will be self-reported.

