#### Self-report questionnaires

##### Sociodemographic and weight history

This history assesses data on the demographic information (sex, age, and marital status) and relevant clinical variables (type of surgery, pre-surgery weight, lowest and highest weight before surgery, lowest weight achieved after surgery).

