### Psychological self-report measures

Repetitive Eating Questionnaire [12]: This self-report questionnaire assesses a grazing-type eating pattern through 15 items, resulting in two subscales that reflect compulsive grazing and non-compulsive grazing subtypes.

Depression Anxiety Stress Scales [36]: This 21-item questionnaire generates subscales on depression, anxiety, and stress.

Eating Disorder – 15 [37]: This 15-item questionnaire assesses eating disorder cognition and behaviors, with subscales for weight and shape concerns and for eating concerns.

Negative Urgency Subscale [38]: This 12-item scale assesses an individual’s tendency to surrender to strong impulses, particularly when accompanied by negative emotions, such as depression, anxiety, or anger.

Influence of weight: Developed by the research team, this 12-item measure inquires about the influence of weight in different areas of life (e.g., intimate relationships, professional roles, self-esteem).

Satisfaction questionnaire: Developed by the research team, this 19-item questionnaire addresses the utility and feasibility of the program from the patient’s perspective.

All questionnaires have been used with this sample by the research team in previous studies, and show good internal consistency for use with bariatric surgery patients.

Table 3 presents a summary of the self-report measures used for each group at each assessment time.

**Table 3 Tab3:** Timeline for the self-report measures

	Registration	Baseline (*T* _b_)	4-month midterm assessment (*T* _m4_)	8-month midterm assessment (*T* _m8_)	Final (end of treatment) assessment (*T* _f_)	6-month follow-up assessment (*T* _fu6_)	12-month follow-up assessment (*T* _fu12_)	Weekly
Sociodemographic weight history	X	–	–	–	–	–	–	–
Clinical inventory	–	X	X	X	X	X	X	–
Repetitive Eating Questionnaire [12]	–	X	X	X	X	X	X	–
Depression Anxiety Stress Scales [36]	–	X	X	X	X	X	X	–
Eating Disorder – 15 [37]	–	X	X	X	X	X	X	–
Negative Urgency Subscale [38]	–	X	X	X	X	X	X	–
Influence of weight	–	X	X	X	X	X	X	–
Satisfaction questionnaire	–	–	–	–	Intervention group	–	–	–
Eating and exercise behaviors (Table 4)	–	Control group	Control group	Control group	Control group	X	X	Intervention group

*X* available for both intervention and control group

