Baseline (*T*_b_), midterm (*T*_m4_ and *T*_m8_), end of treatment (*T*_f_), and follow-up (*T*_fu6_ and *T*_fu12_) data on primary and secondary outcomes will be compared between the two groups. Repeated measures gathered for the intervention group during the feedback messaging system will be used to study the effect of behavior and psychological outcomes on weight. Repeated assessment enables testing of the course of relevant factors and their relation to weight.

Moderators and nonspecific predictor variables that can affect outcomes without stemming from the intervention are assessed at baseline (*T*_b_); these variables include pre-surgery body mass index, type of surgery, sex, severity of general psychopathology, and frequency of maladaptive behaviors.

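### Table 3 gives the eating and exercise items at baseline to controls only, so a secondary outcome that is also a planned moderator has no same-form, pre-allocation baseline in both arms

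*Protocol article*

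**What the plan says.** **Order of steps.** In Informed consent and randomization, participants consent and register online, and then "All participants will complete an initial short sociodemographic and clinical questionnaire". Next, "the APOLO-Bari system will then automatically randomize (computer-generating random numbers) the participants on a 1:1 basis, matching for age, sex, and surgery type". Access comes after that: "After randomization, intervention group members will receive full access to the three components of the APOLO-Bari program in their personal accounts". This section does not place T_b before allocation.

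**Instruments.** Table 3 has separate Registration and Baseline columns. Only the sociodemographic and weight history is marked at Registration; according to its own section it covers demographics and "relevant clinical variables (type of surgery, pre-surgery weight, lowest and highest weight before surgery, lowest weight achieved after surgery". Seven rows have an entry under T_b. Six of them (the clinical inventory and five self-report scales) are marked for both arms. The seventh, which begins "Eating and exercise behaviors (Table 4", is marked for the control group at T_b, at both midterm visits and at end of treatment. The intervention group appears in that row only under Weekly until the follow-up visits, when both arms are marked.

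**Use of the data.** Primary and secondary outcome measures lists days with maladaptive eating as a secondary outcome and plans to compare secondary outcomes between arms at T_b as well as later. It also says: "Moderators and nonspecific predictor variables that can affect outcomes without stemming from the intervention are assessed at baseline". The variables named are "pre-surgery body mass index, type of surgery, sex, severity of general psychopathology, and frequency of maladaptive behaviors". The Statistics section takes pre-intervention self-report scores, and any relevant baseline differences, as covariates.

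**Weight.** "Both the intervention group and the control group will have their height and weight measured by the research team at baseline"; the timing relative to randomisation is not given.

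**The concern.** A form can be given to one arm alone only when allocation is already known. For the Table 4 items, T_b as scheduled therefore follows randomisation, and participants can see which arm they are in.

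The two arms also produce the value in different ways. Controls fill in a stand-alone assessment. Intervention participants make their first entry in a monitoring tool that is part of the treatment and returns a tailored message on submission. A difference between arms at T_b could then reflect chance imbalance, a reaction to allocation, early program use or the mode of collection, and the data could not separate these.

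Two uses suffer directly: the between-arm comparison of days with maladaptive eating, which loses its starting point, and the moderator analysis, which needs a value that treatment cannot have touched. If the other T_b scores are also collected after allocation, the rule of adjusting for baseline differences could adjust for a consequence of allocation. The resulting bias could run in either direction.

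**Working it through.** The article states no figure on this point, so the check sets its sections side by side.

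1. *Is the form given before allocation the same as T_b?* The form contains sociodemographic and clinical questions. The sociodemographic and weight history section includes clinical variables, and Table 3 marks that instrument, and no other, at Registration. The two places agree. The clinical inventory and the psychological scales carry a dash at Registration and first appear at T_b.

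2. *Is T_b after allocation?* For the Table 4 items, yes, by implication: they are reserved for controls at T_b. For the six rows marked for both arms, Table 3 is compatible with either order. The consent section lists the self-report measures among the things controls can access once allocated. That points to T_b after allocation but does not say so.

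3. *What is the intervention arm's first value?* It is the first weekly entry, because the weekly system is one of the three components opened after randomisation. The items look back over 7 days, and the system opens once a week. Suppose the first opening falls *k* days after access and is answered. Then min(*k*, 7) of the 7 recalled days lie after access. With *k* between 0 and 7 (an assumption, since the article gives no start day), that is 0 to 7 of 7 days, or 0 to 100 %.

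4. *How much of the planned analysis is affected?*
   - Instruments with a T_b entry: 7. Arm-specific: 1. Same form in both arms: 7 − 1 = 6.
   - Listed moderators: 5. Fixed or history items (pre-surgery body mass index, surgery type, sex): 3. Self-reported states: 5 − 3 = 2. Of these two, frequency of maladaptive behaviors is affected directly. Severity of general psychopathology is affected only if the both-arm T_b scales also follow allocation.
   - Weight: pre-surgery and nadir weight, used in the regain formula, are registration items. Current weight is not listed at registration; the team first measures it at T_b, by the same procedure in both arms.

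5. *Do the sections agree?* The outcome section needs a T_b value of the behavior counts in both arms, and a moderator that does not stem from the intervention. Table 3 schedules that value in one arm only. The two must be reconciled whatever the order of the other T_b instruments.

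**The case against.** The strongest reply is that the control-only label merely avoids duplicate completion. The intervention group answers the same items every week, so its first entry can serve as T_b, and if it is made on the first day it recalls a week before access. That is a plausible reason for the label, and in that case contamination by program use would be small. But the article does not name the first weekly entry as the baseline, and even a first-day entry is made with allocation known and inside the treatment tool.

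A second reply is that the Repetitive Eating Questionnaire and the Eating Disorder – 15 are given to both arms at T_b and cover related behavior. They help, but as described they yield subscales rather than the day counts named as the outcome.

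A third reply concerns scope, and it largely stands. A reader might infer that all of T_b, including measured weight, follows allocation. The article does not state this, the flow chart is not available here, the Statistics section calls the scores pre-intervention, and the form completed before allocation could be read as including the clinical inventory, although Table 3 lists that inventory only from T_b on. Measured weight has the same form in both arms and is less open to influence than self-report. The log-rank comparison named for the main efficacy question, as described, does not adjust for T_b scores.

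**Conclusion.** The point holds for the Table 4 items. As scheduled, days of grazing, binge eating and overeating have no same-form baseline taken before allocation in both arms, although the plan compares them at T_b and uses their frequency as a moderator. This conclusion rests on reading the control-only label in Table 3 as meant.

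For the other T_b self-report scores, exposure to a known allocation is a reasonable inference that the authors should confirm or rule out. For T_b weight it is only a possibility.

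Three further inferences are not supported:
- *Post-randomisation exclusions.* Patients are screened against the eligibility criteria before the orientation session and consent, and nothing says the T_b clinical inventory revises eligibility.
- *Controls leaving before T_b.* The article gives neither an interval nor a loss rate.
- *A percentage loss of the planned effect.* The shift, the baseline slope and the direction would all have to be assumed. Expressing the loss against the 0.2 effect size would also mean reading 0.2 as a standardised mean difference. That reading needs 786 participants before dropout, which does not fit the planned 180.

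The point should be corrected while recruitment is open. It does not undermine the randomisation itself.

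**What to change.** 1. In Table 3, give the Table 4 items to both arms at T_b, in identical form and outside the weekly feedback system.
2. State in the randomization section that the system releases allocation only after the T_b questionnaires and the team-measured T_b weight are entered. If this is already the practice, say so and correct the control-only entry.
3. For participants already randomised, record the days from allocation to T_b, and add a sensitivity analysis that adjusts only for registration data (demographics, surgery type and weight history).

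The cost is a lock in the randomisation step, a table edit and one extra analysis. The downside is that randomisation waits until T_b is complete, including the weight measurement.

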### Statistics

Pearson’s chi-square tests will be used to analyze significant differences in the proportion of cases with weight regain and in specific outcome variables between the intervention group and the control group. Significant weight regain will be considered when higher than 5 kg. The Kaplan–Meier approach (together with the log-rank test) will be used to answer the main question of efficacy. Repeated-measures analysis of variance (ANOVA) will be conducted to explore differences between the participant groups for different key variables at various time points. The main effect for surgery type will be investigated. Variables such as log-in frequency, task submission, satisfaction with the program, socio-demographics, pre-intervention scores on self-report measures, and time since surgery will be tested as covariates and predictors of outcomes using Cox regression models. Relevant baseline differences will be included as covariates. Hierarchical linear models will be used to investigate different trajectories of relevant variables assessed from *T*_b_ to *T*_fu12._ Hierarchical linear models are the models that best fit unbalanced designs with unequal number of observations (missing data) per subject. Self-report measures (for depression, impulsiveness, eating disorder and eating patterns, body image, and general distress) will be examined by conducting an analysis of covariance to explore interference with weight outcomes. Post-hoc comparisons will be conducted using Tukey’s procedure. Controlled effect sizes will be calculated using the Cohen’s *d* statistic.

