### Safety aspects and ethical considerations

The study is being conducted in accordance with the latest version of the Declaration of Helsinki. Approval from the ethical committees involved (Ethics Subcommittee for Life and Health Sciences, University of Minho; Ethics Committee for Health, Hospital of Braga; Ethics Committee for Health, Hospital Center of São João) were obtained and can be consulted found on the current controlled trials website for our trial registration number. Any trial modifications or the inclusion of new health centers as partners for data collection will be communicated to the ethical committees involved as well as to the trial registration organization. Participation in the research project is entirely voluntary. Participants are informed that their present or future medical treatment will not be affected by their decision to participate or not participate. Participants are informed that they can withdraw from the research project at any time without providing a reason. Participants are assigned a code number to maintain confidentiality. All personal data are stored and handled according to data protection principles. In practice, this arrangement means that the written material will be stored in secure locations, and data stored on the computer will be password protected and encoded (SSL technology) and regularly backed up. Additionally, any publication derived from the personal data will be presented in a way that ensures it is not possible to identify individuals. Communications via internet chat will be protected through encoding (SSL technology).

Our team also shares concerns regarding the identification (by our research team or internet program) of patients who might be under extreme distress. If so, the program or researcher will generate an alert, and the project coordinator will proceed to refer the patients to additional, more specific care in the medical center. Alerts will be generated if: (a) significant weight regain is experienced (≥10 kg since the beginning of intervention); (b) there are maladaptive eating behaviors for at least 3 months with a frequency of at least once a week. A participant under individual support may continue the program unless otherwise requested by the accompanying specialist.

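### Hospital is neither a balancing factor in the randomisation nor a named term in the analysis: a small, cheaply avoided loss (low priority)

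*Protocol article*

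**What the plan says.** Design and procedures states: "Consecutive participants will be recruited from two hospital centers in the North of Portugal". The comparison is between "a treatment-as-usual control group and an intervention group, who receive both treatment as usual and the internet-based program". The content of usual care is not described.

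Informed consent and randomization has the system allocate, by computer-generated random numbers, "the participants on a 1:1 basis, matching for age, sex, and surgery type". Hospital is not listed. Safety aspects and ethical considerations provides for notifying the ethics committees of "the inclusion of new health centers as partners for data collection", so more sites are possible, though not announced.

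In Statistics, Kaplan–Meier, "together with the log-rank test) will be used to answer the main question of efficacy". No stratification is mentioned for that test or for the chi-square comparison of regain proportions. The Cox covariates and predictors are introduced as "Variables such as log-in frequency, task submission, satisfaction with the program, socio-demographics, pre-intervention scores on self-report measures, and time since surgery". The section adds: "The main effect for surgery type will be investigated". The moderators listed under Primary and secondary outcome measures (pre-surgery BMI, surgery type, sex, psychopathology, maladaptive behaviors) also omit hospital. One further sentence in Statistics allows relevant differences at baseline to be carried as covariates.

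**The concern.** Hospital is the usual first candidate for a balancing factor in a multicenter trial, because patients, surgical practice and follow-up can all vary by site. The protocol itself gives a reason to expect hospital to matter. Its Background links few follow-up visits to poor outcome, and its rationale for the program says that sparser appointments let problem behaviors go unaddressed. If the two hospitals differ in follow-up, hospital is prognostic for weight regain.

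Three things are then at stake. The arms may differ by chance in hospital mix. Between-hospital variation stays in the error term of any analysis that ignores it. And if the hospitals differ in the operations they perform, the planned comparison of surgery types is partly a comparison of hospitals. Matching the arms on surgery type does not help with this last point: it makes the arms alike, not the surgery groups.

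**Working it through.** The plan gives no figure on this point to reproduce. The sample size of 180 (90 per arm, Proposed sample size and power calculations) does not depend on hospital and is taken as given.

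**Inputs from the document:** N = 180, 90 per arm, 1:1 allocation, two hospitals.

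**Assumptions (not in the document):** share *p* of patients from the larger hospital, 0.5 to 0.8; difference δ in mean outcome between hospitals, 0.2 to 0.5 within-hospital SD.

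**Step 1: chance imbalance.** With 90 of 180 allocated to each arm without regard to hospital, the number from one hospital in one arm is hypergeometric. The between-arm difference in hospital share then has

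SD = √[4p(1−p)/(N−1)].

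- p = 0.5: √(1/179) = 0.0747, or 7.5 points.
- p = 0.8: √(0.64/179) = 0.0598, or 6.0 points.

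**Step 2: shift in the treatment difference at a one-SD imbalance** = δ × SD of imbalance.

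- Smallest: 0.2 × 0.0598 = 0.012 SD.
- Largest: 0.5 × 0.0747 = 0.037 SD.

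**Step 3: precision lost by ignoring hospital.** Between-hospital variance is p(1−p)δ² in units of the within-hospital variance, so the standard error is multiplied by √[1 + p(1−p)δ²].

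- Smallest: √(1 + 0.16 × 0.04) = 1.003.
- Largest: √(1 + 0.25 × 0.25) = 1.031.

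The tail probabilities below are exact hypergeometric values.

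| Split | SD of imbalance (points) | P(≥10 points) | P(≥15 points) | Shift, δ = 0.2 / 0.5 (SD) | SE inflation, δ = 0.2 / 0.5 |
|---|---|---|---|---|---|
| 50:50 | 7.5 | 18% | 5.2% | 0.015 / 0.037 | 0.5% / 3.1% |
| 60:40 | 7.3 | 17% | 4.8% | 0.015 / 0.037 | 0.5% / 3.0% |
| 70:30 | 6.9 | 14% | 3.4% | 0.014 / 0.034 | 0.4% / 2.6% |
| 80:20 | 6.0 | 9% | 1.5% | 0.012 / 0.030 | 0.3% / 2.0% |

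**Step 4: scale.** The standard error of a two-arm mean difference with 90 per arm is √(2/90) = 0.149 SD. The one-SD shifts are therefore between 0.012/0.149 = 0.08 and 0.037/0.149 = 0.25 of a standard error.

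Two qualifications apply. Step 1 treats allocation as unrestricted with respect to hospital; if surgery type tracks hospital, matching on surgery type already balances hospital in part and the imbalance is smaller. Steps 2 to 4 are for a continuous outcome and only indicate the order of magnitude for the log-rank test.

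**Step 5: can the baseline-difference sentence do the job?** It could put hospital into a regression or covariance model if an imbalance were seen and judged relevant. It does not name hospital, it is triggered by the data, and it cannot act on a log-rank or chi-square test run without strata.

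**The case against.** The strongest reply is that nothing here is wrong. Patients are randomised individually and usual care goes to both arms, so hospital can be unevenly spread only by chance, and the standard error of the unadjusted comparison already allows for that. The program is delivered online rather than by hospital staff, and the research team measures weight, so some usual reasons for balancing by center are weak. The covariate list is open-ended, an analysis plan not shown may name hospital, and the sentence on baseline differences gives a route in.

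Most of this stands, and it rules out three stronger readings:

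- *A hospital imbalance would pass as a program effect, or raise the false-positive rate.* It would not. Chance imbalance in a prognostic factor is part of the sampling error that the test already counts.
- *The comparator is a different treatment at each hospital.* The document does not say so. It leaves usual care undescribed and makes no comparison between hospitals. That contact falls as time since surgery grows concerns time, not site.
- *Nothing planned could correct an imbalance.* The baseline-difference sentence could, within the limits given above.

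What does not fall is the allocation itself. The balancing factors are a stated design choice, and no analysis plan can change allocations already made. The analysis half is softer: if the analysis plan already stratifies or adjusts for hospital, that half is met.

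**Conclusion.** The omission is real and its effect is small. It leaves an avoidable chance imbalance with a standard deviation of about 6 to 7.5 percentage points in hospital share, less if surgery type tracks hospital. The loss of precision is about 0.3% to 3% in the standard error. These figures rest on assumed recruitment splits of 50:50 to 80:20 and an assumed between-hospital difference of 0.2 to 0.5 SD; the document gives neither. A possible further consequence, if the hospitals differ in their mix of operations, is that the surgery-type main effect partly reflects hospital. The document does not support a claim of systematic bias. Priority: low, an optional improvement.

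**What to change.** For all participants, pre-specify a log-rank test stratified by hospital, and a fixed effect for hospital in the Cox, covariance and hierarchical models. This protects those already randomised, removes later discretion over whether hospital counts as a relevant baseline difference, and lets the surgery-type effect be estimated within hospital.

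Trial status says that recruitment is not complete. For participants still to be enrolled, and for any new center, add hospital as a balancing factor in the automated randomisation and record the date of the change.

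The analysis change costs one stratum or one model term. The randomisation change costs one field in an existing system, an algorithm altered during recruitment, and a fourth balancing factor in a trial of 180. If the matching works by strata, adding a two-hospital factor doubles the number of cells. With two sexes, two operations and, as an assumption, two or three age bands, 8 to 12 cells become 16 to 24, or on average 180/16 ≈ 11 down to 180/24 = 7.5 patients each. If that is judged too thin, the analysis change alone recovers most of the benefit.
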